### 2.12. Harm

Adverse reactions (ARs) will be collated as secondary outcomes. At 12 weeks after random allocation, we will specifically ask if participants have had any of the following ARs: headache, nausea, diarrhea, loose stool, and burping (if any, we will also ask about the time of onset, severity, subjective severity, need for treatment, and prognosis). The ARs of the participants in the intervention group will be monitored over the telephone by the CRC at 4 and 8 weeks after entry into the study. This step is based on previous studies reporting an 18% increased risk of ARs with omega 3 supplements compared to a placebo. The most common ARs were gastrointestinal and included nausea, diarrhea, and other minor gastrointestinal disturbances [44]. Clinical trials using Bifidobacterium have been conducted with only small sample sizes, and the ARs remain unclear.

An Efficacy and Safety Committee will be established, comprising an independent chair and at least two independent members. In the event of a serious illness for which a causal relationship to the intervention cannot be ruled out, this Committee will convene. If three serious illnesses for which a causal relationship to the intervention cannot be ruled out occur, the study will be stopped immediately without waiting for review by the Committee. The treatment of and care for ARs in patients enrolled in the study are covered by their medical insurance.

Participants who experience a substantial worsening of FCR or depressive symptoms during the study period will be promptly referred to a psychiatrist in collaboration with their physician. All of the test foods used in this study are commercially available and are well-established dietary products. Therefore, this study will not be covered by clinical research insurance. In the unlikely event that a research subject suffers health problems as a result of participation in this study, appropriate measures will be taken to provide the necessary treatment, including examination and treatment, within the research subject’s insurance coverage.

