### 2.13. Sample Size Calculation

The sample size was estimated based on power analysis using the CARS score. To our knowledge, no previous reports have examined the effects of nutritional interventions on FCR, so there is no reference on which we can base our power calculation.

In our observational study conducted between 2017 and 2018, the mean CARS score of a subset of breast cancer survivors who met the eligibility criteria for this study with a prior history of chemotherapy and CARS score ≥3 was 3.96 (SD ± 0.67). Furthermore, in this study, the intervention will be considered clinically significant if the mean CARS score at week 12 in the intervention group is 1 point lower than the mean CARS score at week 12 in the control group. The CARS score ranges from 1 (not worried at all) to 6 (always very worried). In the opinion of breast surgery specialists (TK and AM), a 1-point decrease in this score from 4 (somewhat worried) to 3 (slightly worried) is clinically significant.

Thus, based on the above hypothesis and the results of our previous study, the mean difference in CARS scores was estimated to be 1.0 ± 0.67 (SD) between the Bifidobacterium plus perilla oil group and the control group and between the Bifidobacterium and the control groups at 12 weeks after random allocation. To detect the difference between the two groups, using unpaired *t*-tests with a one-sided alpha of 2.5% and power of 90%, the calculation showed that 11 participants per group would be required in the analysis population. This was calculated using G*Power software (ver.3.1.9.4). Assuming 4 dropouts per group, 15 participants will be enrolled per group (45 in total).

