The following secondary and sensitivity analyses will be performed for additional discussion of the primary analysis, which will determine the need for further studies. These analyses will be conducted after the primary analysis is completed. For all continuous outcomes (CARS, PHQ-9, IBS-SI, and gut microbiome composition), differences in the scores at 12 weeks and changes between baseline and 12 weeks will be examined using non-paired t-tests and mixed-effect models for repeated measures analysis using repeated timepoints and age, disease duration, and hospital as covariates. For dichotomous or dichotomized categorical outcomes such as ARs and proportion of participants with a moderate or high level of FCR at 12 weeks, relative risk will be calculated. Chi-squared and Fisher’s exact tests will be used for statistical significance testing. The aforementioned analyses will be performed between the combined intervention group (those treated with Bifidobacterium alone and those treated with Bifidobacterium plus perilla oil; *n* = 30) and the control group (*n* = 15). The purpose of this analysis is to increase the power of the hypothesis test to examine whether Bifidobacterium intervention is effective against FCR. This is a supplemental analysis to reinforce the arguments of the primary analysis. Furthermore, to explore the association of changes in symptoms with the gut microbiome and PUFAs, we will perform correlation analyses.

This study will not include an interim analysis. If either of the intervention groups (Bifidobacterium alone and Bifidobacterium plus perilla oil) are inferior to the usual treatment group (control group), it is not a matter of concern whether it is statistically significant or not, so the test will be one-sided. The significance level of the entire test is 2.5% for one side. While this decision might lead to errors in multiple tests, this will be the first study of nutritional intervention for FCR. Therefore, we consider the avoidance of beta errors to be preferable over alpha errors. However, 95% confidence intervals will be presented for differences among groups.

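### Adverse reactions are assigned a relative risk and significance tests that say little with 15 per arm; per-arm counts and risk differences with intervals would serve better (minor)

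*Protocol article*

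**What the plan says.** Section 2.12 (Harm) gives ARs the status of a secondary outcome: "Adverse reactions (ARs) will be collated as secondary outcomes". Participants are asked at 12 weeks about five listed symptoms: headache, nausea, diarrhea, loose stool and burping. The 4- and 8-week monitoring calls are justified by "previous studies reporting an 18% increased risk of ARs with omega 3 supplements compared to a placebo". For the probiotic there is no figure: "Clinical trials using Bifidobacterium have been conducted with only small sample sizes, and the ARs remain unclear".

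Section 2.14 fixes the analysis. For binary outcomes, with ARs named as an example, "relative risk will be calculated". Two methods, chi-squared and Fisher's, are then named for comparing the arms: "exact tests will be used for statistical significance testing". The same analyses are then repeated on pooled arms, 30 v 15: "The aforementioned analyses will be performed between the combined intervention group". The section sets a one-sided 2.5% level and promises 95% confidence intervals for between-group differences.

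Section 2.13 derives the arm size from CARS only: "Assuming 4 dropouts per group, 15 participants will be enrolled per group (45 in total"). No AR incidence and no AR power are stated.

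**The concern.** The plan commits to a measure and a form of inference for ARs, and neither suits arms of 15.

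- A ratio to the control risk does not exist when the control arm has no case, which is likely for an uncommon symptom in 15 untreated people.
- A significance test at this size will almost always return a non-significant result, whether or not there is a moderate excess.

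Section 2.14 says the trial is meant to inform a phase III study, and Section 2.12 says the ARs of Bifidobacterium are unclear. The AR results will therefore be looked at. What is at stake is how they read: a list of missing ratios and non-significant p-values hides how little has been ruled out, whereas an interval shows it.

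**Working it through.** **Inputs from the protocol article.** 15 per arm and 30 v 15 pooled (Sections 2.13, 2.14); one-sided 2.5% (Section 2.14); relative risk 1.18, reading the 18% in Section 2.12 as a relative increase.

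**Assumed.** Control AR incidence, because none is given; a range is shown. The one-sided test is taken in the direction of harm.

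**The plan's own figure.** The only power statement is for CARS. With d = 1.0/0.67 = 1.49, the noncentral t gives 88.4% power at n = 10 per group and 91.4% at n = 11. So 11 is the smallest size reaching 90%, and 11 + 4 dropouts = 15. The stated size reproduces, but it says nothing about ARs.

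**Step 1: is the relative risk defined?** It is not when the control arm has no case. The probability is (1 − p)^15.

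| Control incidence p | No case among 15 controls |
|---|---|
| 5% | 0.95^15 = 46% |
| 10% | 0.90^15 = 21% |
| 15% | 0.85^15 = 9% |
| 20% | 0.80^15 = 3.5% |
| 30% | 0.70^15 = 0.5% |

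This is a problem of rare single symptoms, and it fades by 20%.

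**Step 2: what can the test detect?** Power is the sum, over all pairs of counts with p ≤ 0.025, of Bin(a; n1, 1.18p) × Bin(b; 15, p).

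| Control incidence | 15 v 15, Fisher | 15 v 15, uncorrected chi-squared | 30 v 15, Fisher |
|---|---|---|---|
| 10% | 0.5% | 2.1% | 0.1% |
| 20% | 1.6% | 4.4% | 1.4% |
| 30% | 1.8% | 5.3% | 2.4% |
| 40% | 2.2% | 5.5% | 3.6% |

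Two-sided 5% Fisher tests give much the same at 15 v 15: 2.0%, 2.2% and 2.5% at 20%, 30% and 40%.

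**Step 3: is this only because 1.18 is a small effect?** No. With one-sided Fisher at 15 v 15, a doubling from 20% to 40% has 11% power and a tripling from 10% to 30% has 15%. For 80% power the excess must be about 10% v 64% (with chi-squared, about 10% v 55%). At 30 v 15, 20% v 40% has 16% power.

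**Step 4: what would the alternative show?** The Newcombe interval combines the two Wilson limits and exists with zero cells.

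- 2/15 v 2/15: Wilson limits are 3.7% and 37.9% in each arm. The difference is 0, with half-width √[(0.379 − 0.133)² + (0.133 − 0.037)²] = 0.26, so −26 to +26 percentage points.
- 5/15 v 2/15: difference 20 points, −11 to +47.
- 0/15 v 0/15: the Wilson upper limit is 1.96²/(15 + 1.96²) = 3.84/18.84 = 20%, so −20 to +20 points, where the relative risk has no value.

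**The case against.** The strongest case against has five parts.

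1. *No safety conclusion is planned from these tests.* A reader might infer that a non-significant AR result will be reported as evidence of safety. No section says so. ARs are secondary, and the rule that rejecting the null hypothesis shows effectiveness applies to CARS alone. This stands: false reassurance is a foreseeable misreading, not a stated intention.
2. *Intervals are already promised.* Section 2.14 says 95% intervals will be given for differences among groups. This stands in part. The sentence is general, and the measure named for ARs is a ratio, so nothing ties an interval for a risk difference to the ARs.
3. *The two numerical problems concern different events.* One might read the figures as saying that the relative risk is often undefined and the power is about 2% for the same reaction. They do not: at 20-40% incidence, where power is about 2%, an empty control arm occurs in 3.5% of trials or fewer. One could also multiply across the five listed symptoms as if independent, but four are overlapping gastrointestinal complaints, so the product would overstate the problem. Both points stand.
4. *The 18% is not this trial's target.* It is for omega-3 against placebo, so it bears on the combination arm and not on Bifidobacterium alone. About 2,064 per arm would be needed for 80% power at 20% v 23.6%, and no pilot could offer that. This stands, and the trial is not at fault for lacking that power. Step 3 shows, however, that the test is weak against far larger effects too.
5. *Serious events are handled elsewhere.* Section 2.12 provides an independent committee and a stopping rule that do not depend on p-values. That is so, but these provisions cover serious illness and not the five listed symptoms.

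**Conclusion.** The point holds as a minor improvement (consider), not as an error in the plan. With 15 per arm, the measure named for ARs is often undefined for rare single symptoms (46% of trials at 5% control incidence, 21% at 10%). The tests are nearly uninformative for commoner ones: about 2% power by Fisher for a relative risk of 1.18 at 20-40%, up to about 6% by chi-squared, and 11% by Fisher for 20% v 40%. Pooling to 30 v 15 leaves Fisher power for 1.18 at about 4% or less at incidences up to 40%.

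All these figures depend on assumed control incidences, and the 1.18 scenario applies to the combination arm only. The documents do not support the stronger reading that the protocol will declare the interventions safe on a non-significant test. They show only that the chosen method leaves room for that reading.

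**What to change.** In Section 2.14, take ARs out of the sentence on relative risk and significance tests. For ARs, state instead:

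- counts and percentages in each of the three arms, for each listed symptom;
- the risk difference of each active arm from control, separately, with a 95% Newcombe interval;
- any statement on safety rests on the upper limit of that interval, not on a p-value.

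The relative risk can stay for the dichotomised CARS outcome. Which single test goes with it can be left to the statistical analysis plan. It should be named before the data are seen, because chi-squared and Fisher can disagree in small tables: 4/15 v 0/15 gives one-sided p = 0.016 by uncorrected chi-squared and 0.050 by Fisher.

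The cost is wording only, with no change to sample size, visits or data collected. The downside is that the report must show wide intervals, such as −26 to +26 percentage points for 2/15 v 2/15.

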## 2. Methods and Analysis

### 2.1. Study Design

This study has been planned as an exploratory clinical study (phase 2) and will be conducted as a three-arm, 12-week parallel group, masked-rater randomized controlled trial (RCT). The study is registered in the Japan Registry of Clinical Trials (jRCT; Trial ID jRCTs031200029). Participants will be randomized with 1:1:1 allocation to receive Bifidobacterium plus perilla oil, Bifidobacterium alone, or no intervention (control). A total of 15 participants will be allocated to each arm. These interventions will end within 12 weeks of the registration of each participant. The primary outcome will be FCR severity at 12 weeks as assessed by masked raters using the 4-item Concerns about Recurrence Scale (CARS) that asks about overall fear of recurrence.

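### The only adverse-reaction comparison written down pools two different regimens against control, for a reason that concerns efficacy alone; by-arm results should be stated

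*Protocol article*

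**What the plan says.** Section 2.14 (Statistical Methods) sets relative risk, with chi-squared and Fisher's exact tests, for "dichotomous or dichotomized categorical outcomes such as ARs" and for the proportion with moderate or high fear of recurrence at 12 weeks. The next sentence fixes the comparison: "The aforementioned analyses will be performed between the combined intervention group", made up of the Bifidobacterium-alone arm and the Bifidobacterium-plus-perilla-oil arm (n = 30), and the control arm (n = 15). The purpose given is greater power "to examine whether Bifidobacterium intervention is effective against FCR", and the pooled analysis is described as supplemental to the primary one. The section also promises 95% confidence intervals for differences among groups, without naming the groups.

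Section 2.12 (Harm) makes ARs a secondary outcome. It bases AR monitoring on "previous studies reporting an 18% increased risk of ARs with omega 3 supplements compared to a placebo", and says that for Bifidobacterium the ARs are unclear because its trials were small. Section 2.6 gives perilla oil to one active arm only. The Introduction says that the study will also explore which of the two regimens is preferable.

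**The concern.** Pooling has some logic for efficacy, because both active arms take Bifidobacterium and the stated question is whether Bifidobacterium works. For harm the question is different. The two arms differ by one product, that product belongs to the only class for which the protocol cites an AR figure, and the AR risk of the shared product is described as unknown. A single relative risk for the pooled 30 does not belong to either regimen.

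The trial is meant to inform a phase III study and to explore which regimen to carry forward. That needs tolerability by regimen. By-arm comparisons with control are written out for the primary outcome (Sections 2.13 and 2.14), but not for ARs.

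**Working it through.** **Plan's own figure.** The only sample-size calculation concerns the CARS score, not ARs. Inputs from Section 2.13: "the mean difference in CARS scores was estimated to be 1.0 ± 0.67 (SD"), and "one-sided alpha of 2.5% and power of 90%, the calculation showed that 11 participants per group would be required in the analysis population". The standardised difference is 1.0/0.67 = 1.49. Exact power of the unpaired t-test at one-sided 2.5% is 88.4% with 10 per group and 91.4% with 11, so 11 is reproduced. Adding 4 dropouts gives 15 per group and 45 in total, as stated. No AR rate or AR power is given.

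**What pooling does to the relative risk.** Let p0, pB and pO be the AR risks in the control, Bifidobacterium-alone and Bifidobacterium-plus-oil arms. With 1:1:1 allocation and 15 per arm:

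- pooled risk = (15 pO + 15 pB)/30 = (pO + pB)/2
- pooled RR = (RR of oil arm + RR of Bifidobacterium-alone arm)/2

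The 1.18 is the figure cited in Section 2.12; the other relative risks are illustrations.

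| RR, oil arm | RR, Bifidobacterium alone | Pooled RR |
|---|---|---|
| 1.18 | 1.00 | 1.09 |
| 2.00 | 1.00 | 1.50 |
| 3.00 | 1.00 | 2.00 |
| 2.00 | 1.50 | 1.75 |
| 1.18 | 1.18 | 1.18 |
| 1.18 | 1.50 | 1.34 |

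The first three rows show an oil-only excess being halved. The fifth is the one case in which the pooled figure is right for both arms. In the last row it is too high for the oil arm and too low for Bifidobacterium alone.

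**Power.** The control AR rate is not in the document, so 10%, 20%, 30% and 40% were assumed. Fisher's test at one-sided 2.5%, by exact enumeration:

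| Scenario | Control 10% | 20% | 30% | 40% |
|---|---|---|---|---|
| Oil-arm RR 2.0: oil arm v control, 15 v 15 | 4.0% | 11.1% | 22.7% | 44.7% |
| Same, pooled 30 v 15, Bifidobacterium-alone RR 1.0 | 0.6% | 4.4% | 8.8% | 16.1% |
| Same, pooled 30 v 15, Bifidobacterium-alone RR 2.0 | 3.0% | 16.1% | 37.7% | 65.7% |
| Oil-arm RR 1.18: oil arm v control, 15 v 15 | 0.5% | 1.6% | 1.8% | 2.2% |
| Same, pooled 30 v 15, Bifidobacterium-alone RR 1.0 | 0.1% | 0.9% | 1.5% | 2.1% |

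A much larger effect shows the same dependence. With control at 10% and the oil arm at 50% (RR 5), two-sided 5% Fisher power is 54% by arm. Pooled, it is 25%, 52% or 76% when Bifidobacterium alone is at 10%, 30% or 50%.

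**Precision.** SE(log RR) = √[(1 − p1)/(n1 p1) + (1 − p0)/(n0 p0)], and the 95% interval runs a factor exp(1.96 SE) each way. For the oil arm v control at RR 1.18:

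- control 10%: √[0.882/1.77 + 0.9/1.5] = 1.048, a factor of 7.8
- control 40%: √[0.528/7.08 + 0.6/6] = 0.418, a factor of 2.3

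For the pooled comparison, with Bifidobacterium alone at RR 1.0, the factors are 6.2 and 2.1.

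**The case against.** The strongest reply is that the pooled analysis is labelled supplemental. Such an analysis is added to others, and nothing says that ARs will not be shown by arm. A three-arm trial whose primary analysis is by arm most naturally intends its secondary analyses by arm as well, with pooling on top. AR tables by arm are also the kind of detail that an article leaves to the full protocol. All of this stands against the inference that pooling is the only AR analysis, or that the regimen would be chosen with no harm data by arm. It does not remove the point: the article does fix a grouping for ARs, that grouping is the pooled one, and its stated reason is not about harm.

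Three other inferences are tempting and unsupported:

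- **Any harm from perilla oil is diluted.** This is true only if Bifidobacterium alone carries less AR risk than the combination. Section 2.12 calls that risk unclear, not nil.
- **Pooling costs power.** It does if Bifidobacterium alone is harmless, but where both arms carry the excess, pooling can gain power (44.7% by arm against 65.7% pooled, in the table above).
- **Perilla oil has a known AR excess that pooling would hide.** The 18% is for omega-3 supplements in general, and at this size it is undetectable with or without pooling.

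**Conclusion.** The point holds as a badly fixed comparison. Read literally, Section 2.14 applies the pooled 30 v 15 comparison to ARs and spells out no other. The resulting relative risk averages two regimens and is correct for each only if their risks are equal, which Section 2.12 gives no basis to assume. If the excess lies in the oil arm alone, half of it is lost (1.18 to 1.09, 3 to 2); otherwise the error can go either way. The averaging assumes equal numbers in the two active arms; with unequal numbers the weights change, but the argument does not. The power figures rest on assumed control rates of 10% to 40%. What is at stake is an interpretable estimate for each regimen, not the power to detect the cited 18%.

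**What to change.** In Section 2.14, say that the pooled comparison serves its stated efficacy purpose, and add that ARs are tabulated for each of the three arms with the risk in each. Give the relative risk with 95% confidence interval for each active arm against control, and, descriptively, for Bifidobacterium plus perilla oil against Bifidobacterium alone. That last contrast isolates the oil, and Section 2.12 plans week-4 and week-8 AR calls for participants on intervention and not for controls, so it is also the contrast with like ascertainment. It does not conflict with the decision not to compare the active arms, which is limited to the primary analysis. If a pooled AR figure is kept, label it as additional and as an average over two regimens.

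The cost is a sentence or two of wording and one table by arm, with no new data, participants or procedures. Intervals by arm are generally wider than the pooled one: for an oil-arm relative risk of 1.18 at a 10% control rate, a factor of 7.8 each way against 6.2.

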Probiotics are live microorganisms that confer health benefit on the host when administered in adequate amounts (FAO/WHO Joint Working Group, 2001). Numerous studies have reported improved symptoms in patients with psychiatric disorders following probiotic interventions [20,21,22,23,24,25], and there is growing evidence of an interaction between omega-3 PUFAs and gut microbiota [26,27,28,29]. Diets rich in fish oil, which includes omega-3 PUFAs, increase *Bifidobacterium* levels and decrease Bacteroid levels compared to a diet rich in corn and beef fat [30]. Fat-1 transgenic mice engineered with the *Caenorhabditis elegans* Fat-1 gene can produce omega-3 PUFAs from Omega-6 PUFAs in their organs and tissues. The Fat-1 transgenic mice showed more production and secretion of intestinal alkaline phosphatase (IAP) than mice fed omega-6 PUFAs; the IAP decreased LPS production and gut permeability and suppressed endotoxemia and inflammation [31]. However, no studies have examined the effects of the combination of probiotics and omega-3 PUFAs to date.

This pilot study primarily aims to evaluate the efficacy and effect size of taking perilla oil rich in omega-3 PUFAs and *Bifidobacterium* as a probiotic on FCR in breast cancer survivors after they have completed chemotherapy. We believe the preliminary results will help to guide future full-scale confirmatory trials on their effects. Given the growing interest in the interaction between omega-3 PUFAs and intestinal flora, this study will also explore the optimal dosing regimen (*Bifidobacterium* alone vs. *Bifidobacterium* plus perilla oil).

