### 2.8. Control Group

There will be no placebo capsule or sachet in this phase II trial. The reasons for this are detailed in Section 4. Participants in the control group will not receive any intervention during the study period. Although there will be no restriction on concomitant drugs/treatments/procedures, information regarding concomitant drugs/therapies used during the study will be collected as study data. Whenever inquiries are received from participants, the necessary information will be provided to them.

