### 2.14. Statistical Methods

This study is a phase II trial primarily focused on the effects of Bifidobacterium and perilla oil when taken properly. Therefore, the main analysis will be performed in a per protocol set (PPS), which is defined as participants who complete the final post-intervention primary outcome assessment and complete the protocol-specified interventions. Completion of the protocol-specified interventions is defined as completion of least 4 of the 12 weeks of Bifidobacterium and perilla oil administration; these participants will be considered to have completed the protocol-specified interventions based on a meta-analysis of probiotic interventions for anxiety symptoms where the minimum treatment period in studies demonstrating efficacy was 4 weeks [45].

In the secondary analysis, analysis will be performed on all randomized cases based on the intention-to-treat (ITT) principle, and discrepancies in the analysis using the PPS will also be examined. Regarding patient background, summary statistics (mean, standard deviation, and frequency) will be calculated based on the characteristics of the items, and the presence or absence of bias in the three baseline groups in each item will be evaluated based on analysis of variance or the chi-squared test.

The objective of the primary analysis of this study is to collect data to inform a main confirmatory clinical trial (phase III). Regarding the primary outcome, the primary hypothesis is that the mean CARS scores of the intervention groups (Bifidobacterium alone or Bifidobacterium plus perilla oil) at week 12 will be significantly lower than those of the control group. The intervention will be considered effective if the null hypothesis is rejected. The difference in the mean CARS score at 12 weeks after random allocation between the intervention groups and the control group will be analyzed using the unpaired t-test. In the primary analysis, we will not compare the effects between the two intervention groups. Missing values or modeling will not be imputed for primary analysis. Sensitivity analyses will be performed for the primary outcome after imputing missing data using the multiple imputation method.

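### The supplemental pooled analysis is presented as a test of Bifidobacterium but mixes in half of any perilla oil effect, and the regimen comparison raised in the Introduction is not named in any stated analysis

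*Protocol article*

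**What the plan says.** The trial has three equal arms: Bifidobacterium plus perilla oil, Bifidobacterium alone, and no intervention (Section 2.1). No arm receives perilla oil without Bifidobacterium, and the control is untreated: "There will be no placebo capsule or sachet in this phase II trial" (Section 2.8).

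The Introduction sets a regimen question. It says that "this study will also explore the optimal dosing regimen" and identifies the comparison as Bifidobacterium alone against Bifidobacterium plus perilla oil.

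Section 2.14 tests the intervention groups against control with unpaired t-tests and adds: "In the primary analysis, we will not compare the effects between the two intervention groups". It then lists secondary analyses (t-tests, mixed models, relative risks) and continues: "The aforementioned analyses will be performed between the combined intervention group", 30 participants, and the 15 controls. The reason given is: "The purpose of this analysis is to increase the power of the hypothesis test to examine whether Bifidobacterium intervention is effective against FCR". The same paragraph calls this analysis supplemental and says that it is meant to strengthen the argument from the primary analysis. The section ends with a general undertaking to report 95% confidence intervals for differences among groups.

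**The concern.** The pooled analysis has a stated purpose that it does not serve. Half of the pooled group takes a second active component, so a positive result may come from Bifidobacterium, from perilla oil, or from both. It isolates Bifidobacterium only if perilla oil adds nothing. The article's own rationale points the other way: the Introduction reports lower fear of recurrence with higher blood alpha-linolenic acid, and Section 2.6 chooses perilla oil for its alpha-linolenic acid content.

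The second issue is a gap between an aim and the stated analyses. Combination against Bifidobacterium alone is the only randomized contrast that isolates perilla oil (given Bifidobacterium), and it is the question that the Introduction asks. Section 2.14 sets it aside for the primary analysis and does not name it elsewhere. Comparing the two p-values against control is no substitute, because one arm can be significant and the other not without the regimens differing.

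The trial is meant to inform a phase III study, so it matters which component is credited with an effect.

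**Working it through.** **Inputs.** Section 2.13 gives a difference of 1.0 and SD 0.67 for each active arm against control, an unpaired t-test at one-sided 2.5% with 90% power, 11 analysable per arm, and 15 enrolled per arm after allowing for 4 dropouts. Section 2.14 gives 30 vs 15 for the pooled contrast. If each arm loses 4, this becomes 22 vs 11. The effect of adding perilla oil is not given, so a range is assumed.

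**1. The plan's own figure.** The noncentrality is 1.0 / (0.67 × √(2/n)). At n = 11 this is 1.0 / 0.286 = 3.50 on 20 df, and exact power is 91.4%. At n = 10 power is 88.4%. So 11 per group reproduces, and 11 + 4 = 15, × 3 = 45. At 15 per arm power is 97.6%.

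**2. What the pooled contrast estimates.** Let β be the reduction in CARS from Bifidobacterium and π the further reduction from adding perilla oil. The expected difference is

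[n_B × β + n_C × (β + π)] / (n_B + n_C),

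where n_B and n_C are the sizes of the Bifidobacterium-alone and combination arms. With n_B = n_C this equals β + π/2. With unequal losses the weight on π shifts away from one half.

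**3. Rejection when Bifidobacterium does nothing (β = 0).** Results are from 100,000 simulated trials per row and size, SD 0.67 in every arm, pooled-variance t-test, one-sided 2.5%.

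| Assumed π (points) | 30 vs 15 | 22 vs 11 |
|---|---|---|
| 0 | 2.4% | 2.5% |
| 0.25 | 7.9% | 6.8% |
| 0.5 | 18.4% | 14.2% |
| 1.0 | 49.9% | 36.3% |

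**4. What pooling gains.** If both active arms have the planned 1.0-point effect, power rises from 97.6% to 99.6% (15 per arm) or from 91.4% to 97.4% (11 per arm). If both have 0.5 points, it rises from 50.5% to 63.6% at 15 per arm. If Bifidobacterium gives 0.5 points and the combination 1.0, the pooled test rejects in 92.0%. The step from 63.6% to 92.0% is due to perilla oil.

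**5. The regimen contrast (combination minus Bifidobacterium alone, unadjusted).** The 95% half-width is t(0.975, 2n − 2) × 0.67 × √(2/n):
- 11 per arm: 2.086 × 0.286 = 0.60
- 15 per arm: 2.048 × 0.245 = 0.50

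| Assumed π (points) | Power, 15 per arm | Power, 11 per arm |
|---|---|---|
| 0.25 | 16.5% | 13.0% |
| 0.5 | 50.5% | 38.4% |
| 1.0 | 97.6% | 91.4% |

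The difference detectable with 90% power is 0.82 points (15 per arm) or 0.97 (11 per arm). Ninety per cent power for 0.5 points would need 39 per arm.

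**The case against.** **The attribution risk is already contained.** Bifidobacterium alone against control is a primary comparison and involves no perilla oil. The pooled analysis follows it as a supplement. With a null Bifidobacterium effect, the Bifidobacterium-alone test rejects in 2.5% of trials, so both tests are falsely positive together in at most 2.5%. This stands. A reader might infer from the table that the trial has up to a 50% chance of wrongly crediting Bifidobacterium. The documents do not support that: the rate applies to the pooled test read alone, under the most extreme scenario shown. What remains is that a contrast containing perilla oil cannot reinforce the Bifidobacterium result in the way the article says.

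**The regimen comparison may be planned.** A reader might infer that it is ruled out. Section 2.14 excludes it only from the primary analysis, the secondary methods are listed before pooling is mentioned, and the closing promise of confidence intervals among groups could cover it. The article also condenses a fuller protocol that is not shown. This stands too, so the point is confined to what the text supports: no stated analysis names the comparison, although the Introduction names the question.

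**The estimate would still be obtainable.** Both arms share one control group, so the difference between the two arm-versus-control estimates is the regimen contrast, and its interval follows from the arm means and SDs. It would therefore be wrong to say that the trial must end without it. What is lacking is its designation and status.

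**The contrast is imprecise.** This is correct. An interval of ±0.5 to ±0.6 points does not ensure a choice between regimens, and if the arms have the equal effects assumed in Section 2.13 it will not separate them. It supports estimation only.

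**Conclusion.** The point holds in two limited parts.

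First, the stated purpose of the pooled analysis is wrong by design. With equal arms it estimates the Bifidobacterium effect plus half of any perilla increment, and it tests Bifidobacterium only if that increment is zero. Under a null Bifidobacterium effect, the pooled rejection rate at 30 vs 15 runs from about 8% to 50% for assumed perilla effects of 0.25 to 1.0 points (7% to 36% at 22 vs 11). These figures assume normal scores with SD 0.67 in every arm. The perilla effects are assumptions, because the article gives none.

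Second, the regimen question in the Introduction is not tied to any named analysis.

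The primary comparisons and the sample size are unaffected. The severity is minor to moderate, since the trial is exploratory, the pooled analysis is supplemental, and a perilla-free test of Bifidobacterium is already primary. That test is itself against an untreated control, a limitation that the article acknowledges in its Discussion.

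**What to change.** 1. In Section 2.14, relabel the pooled analysis as any Bifidobacterium-containing regimen vs no intervention. Delete the sentence saying that it examines whether Bifidobacterium is effective, and state that this conclusion rests on Bifidobacterium alone vs control.
2. Name combination minus Bifidobacterium alone as a secondary estimate for CARS, with a 95% confidence interval. Describe it as exploratory, without an efficacy claim, and not powered for a modest increment. Give the expected unadjusted half-width: about 0.5 points at 15 per arm and 0.6 at 11 per arm.

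The cost is a wording change and one further contrast on data already collected. No new arm, assessment or participant is needed.
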